### Interventions

Participants in both intervention arms receive: 1) targeted and tailored dietitian-administered counseling at the CTRC; 2) access to an intervention-specific website; and 3) a continuous supply of food items with precisely quantified fatty acid compositions formulated to meet nutrient intake targets. Participants meet with the research dietitian approximately every 14 days throughout the 12-week dietary intervention to receive diet education, a 2-week supply of research foods, and a dietary adherence assessment. Meal plans and recipes that meet the nutrient intake targets are provided, as well as specific instructions on how to meet the diet targets and what foods to purchase in addition to those provided by the study. Study-provided foods are selected based on fatty acid analysis completed by the Section on Nutritional Neurochemistry, Laboratory of Membrane Biochemistry and Biophysics, NIAAA/NIH. Research foods are procured and prepared by the Nutrition Research and Metabolism Core of the Clinical and Translational Research Center at UNC, which is supported in part by grant UL1RR025747 from the National Center for Research Resources, National Institutes of Health.

Participants in both diet groups are educated on how to limit LA and AA in their diets. Because most available US oils contain substantial amounts of LA, participants are provided with, and instructed to use, only low LA oils and fat sources (e.g. macadamia nut oil, coconut oil, low-LA olive oil, butter, fat-free mayonnaise, specified salad dressings). Nutrient analysis performed on numerous brands of each of the above oils and fat sources ensured the selection of those with the lowest LA content.

Participants randomized to the low n-6 plus average n-3 diet group are instructed to reduce their intake of AA by restricting consumption of egg yolks, organ meats, meats, and certain fish. They are asked to eat up to 2 vegetarian meals per day, and up to 1 meal per day that includes very lean (low n-3) fish or shellfish and/or egg whites. Study foods provided to low n-6 dieters include several types of canned beans, frozen lean seafood (e.g. shrimp, grouper, cod, very low-fat chunk light tuna), and low-fat turkey slices, chosen on the basis of nutrient analyses to achieve the lowest amounts of n-3 EPA+DHA and n-6 AA.

Study participants randomized to the low n-6 plus high n-3 diet are instructed to consume 14 g of ground flaxseed each day, to reach the nutrient intake target for n-3 ALA (Table 1). They receive ground flaxseed or prepared flaxseed products to include granola, muffins, granola bars and bean dip. To reach EPA and DHA nutrient intake targets, the low n-6 plus high n-3 dieters are counseled to consume 1-2, 4 oz servings of fatty fish per day. They are provided with high n-3 canned tuna, canned salmon, frozen salmon fillets, frozen trout and sardines. Nutrient analysis of numerous seafood sources enabled selection of foods with the highest amounts of n-3 EPA+DHA.

Participants in both diet groups are given breads, crackers, tortillas, popcorn, yogurt, string cheese, frozen fruits and vegetables, beans, and prepared vegetarian chili. These carefully-selected study foods displace high LA foods and facilitate adherence with study diets. Web-based intervention materials complement and reinforce dietitian advice. Diet education materials include: 1) Diet Guidelines; 2) Seven-day Meal Plan; 3) Grocery Shopping Guides; 4) Dining Out Guide; 5) Food Lists; and 6) more than 50 recipes that either utilize the study provided foods or meet study guidelines.

Participants complete self-reported outcome assessments at baseline, at their first intervention visit, and at the end of the intervention. They have blood drawn for biomarkers at the first intervention visit (Week 6), and again at weeks 10, 14, and 18. The research staff validates data through weekly contact with participants.

### Masking

Because of the nature of the interventions, the research dietitian cannot be masked to treatment condition. Similarly, participants are aware of the foods included in their diets. However, participants do not have access to information about the other diet. In addition, steps are taken to ensure that credibility of both dietary interventions is maintained. A questionnaire assessing the credibility of both diets as an intervention for headache is administered after the first visit with the dietitian. All investigators except the research dietitian are masked to treatment assignment. Similarly, participants' personal physicians are masked to treatment assignment.

### Remuneration

Participants receive 12 weeks of dietary treatment at no cost. During these 12 weeks, participants receive food for 2 meals and 2 snacks per day, supplied every other week by the CTRC research kitchen. Participants completing the study receive $145 in compensation in addition to costs of mileage and parking of up to $13 per visit.

### Outcome measures and study instruments

#### Primary Outcomes

The primary outcome (Aim 1) is the change in percentage of n-6 in HUFA in total HUFA (%n-6 in HUFA) in plasma and erythrocyte lipid pools, from pre-intervention (Week 6 - end of baseline phase) to post-intervention (Week 18). For determination of the %n-6 in HUFA, fatty acids that are at least 20 carbons in length with 3 more double bonds are considered to be HUFAs. The equation for calculation of %n-6 in HUFA is 100 × (20:3n-6 + 20:4n-6 + 22:4n-6 + 22:5n-6)/(20:5n-3 + 22:5n-3 + 22:6n-3 + 20:3n-6 + 20:4n-6 + 22:4n-6 + 22:5n-6 + 20:3n-9). For Aim 2, we examine the rate of change in %n-6 in HUFA over the 12 weeks of the intervention as measured at Study Week 6, Week 10, Week 14, and Week 18 (Weeks 0, 4, 8, and 12 of the intervention phase).

#### Secondary Laboratory Outcomes

Secondary laboratory outcomes include individual n-6 and n-3 fatty acids in plasma and erythrocyte lipid pools, including n-6 linoleic acid (18:2n-6) and AA, as well as n-3 EPA and DHA. Lipid mediators derived from n-6 AA, EPA and DHA (e.g. eicosanoids, docosanoids), and mediators that may be indirectly influenced by n-6 and n-3 HUFA status (e.g. cytokines, pro-inflammatory enzymes, substance P), will be measured at study completion.

Changes in inflammatory gene expression in peripheral blood mononuclear cells (PBMCs) will be assessed in an additional pilot study. We will test: (1) the effects of the low n-6 diet compared to baseline dietary conditions (gene expression before the dietary intervention); (2) the effects of the low n-6 + high n-3 diet compared to baseline; and (3) the effects of the low n-6 versus the low n-6 + high n-3 diet compared to baseline. PBMCs are isolated from whole blood and RNA will be extracted utilizing Qiagen RNeasy Micro Kit (Valencia, CA). The RNA yield will be quantified with Nanodrop ND 1000 spectrophotometer (Nanodrop Technologies, Wilmington, DE), and integrity will be measured with an Agilent 2100 Bioanalyzer with RNA 6000 Nano chips (Santa Clara, CA). The expression of 84 key genes involved in the inflammatory response will be assessed using the Human Inflammatory Cytokines & Receptors RT² Profiler PCR Array (SA Biosciences, Frederick, MD).

#### Clinical outcomes

Although this study is not powered to assess changes in clinical endpoints, we are measuring the following outcomes in preparation for a larger, fully powered trial of clinical efficacy (Table 3):

**Table 3 T3:** Summary of measures and timing of administration for exploratory analgesic dietary intervention for chronic daily headache as of May 2010

Variable or Instrument	Usual Care - UC Weeks 0 to 6	UC + Diet Weeks 6 to 18
***Primary outcome***		

Headache QOL - HIT-6 §	Week 0, Week 6	Week 18
***Secondary outcomes***		

Headache Diary: Frequency	Daily	Daily
Perceived clinical change	Week 0, Week 6	Week 18
Headache disability - MIDAS#	Week 6	Week 18
Headache Diary: Intensity/Duration	Daily	Daily
Headache Diary: Sleep Duration	Daily	Daily
Headache Diary: Medication Use/Cost	Daily	Daily
Headache Diary: Health care visits	Daily	Daily
Satisfaction with care	Week 0, Week 6	Week 18
Psychological health: BSI-18	Week 0, Week 6	Week 18
Health status: Rand SF-12	Week 0, Week 6	Week 18
***Process measures***		

Nutritional and Metabolic Biomarkers	Week 6	Weeks 10, 14, and 18
Dietary Intake Assessment	Week 5-6	Week 16-18
Food Intake Diary		3 days every 4 weeks
BMI, BP, Weight	Week 5-6	Weeks 10, 14, and 18
***Effect modification measures***		

Demographics	Week 0	
Clinical Characteristics	Week 0	
Expectation of benefit†		After dietary instruction

*International Classification of Headache Disorders, defined by expert members of the International Headache Society

† Based on a measure developed by Borkovec and Nau to measure credibility of psychological interventions.

§ Headache Impact Test was developed to measure headache-related quality of life.

# Migraine disability assessment score assesses the number of days of missed work or school in the past 3 months.

(1) Headache frequency and intensity, medication use, cost of medication, and health care utilization, all collected by self-report in a detailed daily headache diary [34]. The diary, available to participants on a secure website, collects data on headache intensity (none, mild, moderate, severe) and associated aura for every hour of the day and night.

(2) Headache-specific quality-of-life, measured through the Headache Impact Test (HIT-6) [35] at the time of randomization and after completion of the intervention. The HIT-6, with good internal reliability [36], covers functioning relevant to headache-related disability: pain, social functioning, role functioning, vitality, cognitive functioning, and psychological distress. A decrease of 2.3 HIT points (95% CI, 0.3 to 4.3) over 6 weeks among patients with chronic headache corresponds to a "somewhat better" self-reported rating on a global clinical change scale [36].

(3) Headache-related disability, measured with the Migraine Disability Assessment Questionnaire (MIDAS) [37,38] pre-randomization and at the end of the 12-week intervention. Derived from the Headache Impact Test, MIDAS is a 7-item questionnaire that assesses the number of days during the previous 3 months that respondents missed work or school, experienced decreased productivity at work or home, or missed social engagements because of headaches [38]. Test-retest reliability and internal consistency are acceptable (r_2_: 0.67-0.73; alpha = 0.83) [39].

(4) General health-related quality-of-life (SF-12) is measured with a shorter version of the popular Medical Outcomes Study Short Form Health Survey (SF-36) that yields a summary score for mental components and physical components [40]. The SF-12 was found to be reliable, valid, and responsive to change in a population of chronic-back-pain patients [41], and has been employed in migraine research [42].

(5) General psychological distress as measured with the Brief Symptom Inventory (BSI-18), a short (18-item) version of the Symptom Checklist-90-R (SCL-90-R) [43]. Subjects are asked to rate how much they were bothered in the last 7 days by each of 18 symptoms, including separate scores for anxiety, depression, somatization, and a global symptom severity index. The BSI has good internal consistency and test-retest reliabilities (alpha = 0.71-0.85; r = 0.68 - 0.91)[44].

#### Possible effect modifiers

Effect modifiers consist of demographics and headache-history variables such as: (1) clinical characteristics of headache over time; (2) use of prescribed and over-the-counter medications; (3) associated medical conditions; (4) family history of headache and other disorders; and (5) a single-item assessment of satisfaction with care. Subject credibility and expectations are assessed using an instrument adapted from a validated scale developed by Borkovec and Nau [45,46] and administered just after the first intervention visit. Because high expectations of treatment are closely related to better outcomes [47,48], data analysis will test whether participants in the 2 groups have similar or different expectations of benefit.

#### Process Measures

The research dietitian collects a 3-day food record on visit 3 and daily food-intake checklists every 2 weeks thereafter. Each week, participants rank their diet adherence on a scale of 1 to 5. The research dietitian rates diet adherence on a scale of 1 to 5 based on the study-diet nutrition counseling session every other week. Dietary intake assessments (24-hour recall) are performed on 3 non-consecutive days during the baseline phase and repeated during the final 3 weeks of the intervention phase. Blood samples are obtained for fatty acid analysis at baseline and every 4 weeks during the intervention phase.

### Quality control

All personnel complete lab safety training and step-by-step instruction in lab processing. Research assistants record the times that the sample is drawn and the time of each processing step, including the time to centrifuge and time to freezer (-80 F or liquid N tank) storage (Eppendorf) tubes. Each specimen is bar-coded, and triple-recorded to ensure accurate identification. For metabolites sensitive to time, expedited processing ensures good sample quality.

### Adverse events

Reports of adverse events are obtained from participants at each intervention visit, from self reports recorded in the headache diaries, or by direct contact via email or phone with study staff. Adverse events are investigated by the study neurologist and are reported to the UNC Institutional Review Board.

### Statistical Analysis

#### Overview

This study is a 2-arm intervention trial with a baseline measurement and with repeated measures of the outcome variable over time. The primary outcome variable is %n-6 in HUFA after dietary interventions. To correct for violations of the underlying assumptions of regression (e.g., normality, variance homogeneity), we plan to use a transformed value of the proportions as our dependent variable (angular, logit, or power transformation). We plan to invoke intent-to-treat analysis in dealing with missing data.

#### Analysis of Aim 1

In Aim 1, we will assess the extent of lowering %n-6 in HUFA after 12 weeks of targeted dietary interventions. All participants contribute specimens at randomization (week 6), and at weeks 10, 14 and 18. As a first step, we will test the equality of the transformed mean proportions after 12 weeks of the intervention with a t-test and will use the transformed proportions in a regression model to compare the treatment effects adjusting for covariates, including the baseline proportion and other variables that may influence the accumulation and turnover of LA in adipose tissue, such as age, sex, and baseline BMI.

#### Analysis of Aim 2

To test Aim 2, we will make use of the repeated measures of the outcome variable measured at 6, 10, 14, and 18 weeks to compare the rate of reduction in the %n-6 in HUFA over time in the 2 groups. Because the measurements within each person over time are correlated, we will use a hierarchical linear model with transformed proportions as the outcome variable. The first-level model specifies the outcome as a linear function of time. In the second level, the slope and intercept will be a linear function of the treatment variable. The random effects will represent the within- and between-group variances. The regression coefficients of the time-by-treatment terms are of interest here. If the regression coefficients of the interactions are not statistically significant from zero, we will conclude that the rate of change in the outcome variable over time is the same in both groups.

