Adherence with the daily diary has been excellent, with 83.3% of participants completing at least 80% of daily entries. Most have tolerated the diets well; they have demonstrated diet adherence via changes in erythrocyte fatty acids. Preliminary analysis of composite erythrocyte fatty acid data of the first 20 participants, with blinding preserved (i.e., both diet groups are analyzed together and investigators remain masked to diet group), reveals significant reductions in %n-6 in HUFA and n-6 AA and LA, and significant increases in n-3 EPA, DHA and the omega-3 index compared with baseline erythrocyte fatty acids over the 12-week intervention (Table 5).

**Table 5 T5:** Means of erythrocyte fatty acids over the 12-week intervention, Chronic Daily Headache study, May 2010

	Baseline (n = 20)		Week 4 (n = 20)		Week 8 (n = 20)		Week 12 (n = 18)	
	
Variable	Mean	95% CI	Mean	95% CI	Mean	95% CI	Mean	95% CI
Omega-3 index	4.4	3.9, 5.0	6.2	5.4, 7.1	7.0	5.9, 8.1	7.8	6.5, 9.0
% n-6 in HUFA*	76.3	74.5, 78.0	70.4	67.5, 73.2	67.4	63.7, 71.0	64.7	60.3, 69.0
DHA	4.0	3.5, 4.5	5.2	4.5, 5.8	5.7	4.9, 6.5	6.3	5.4, 7.3
EPA	0.46	0.39, 0.54	1.1	0.8, 1.3	1.3	0.95, 1.6	1.4	1.0, 1.8
AA	14.8	14.5, 15.2	14.4	13.7, 15.1	13.8	13.2, 14.5	13.7	12.9, 14.5
LA	11.5	10.8, 12.1	9.5	8.8, 10.2	9.3	8.6, 10.0	9.5	8.8, 10.3

* %n-6 in HUFA is the percentage of omega-6 fatty acid in total HUFA as calculated by: 100 × (20:3n-6 + 20:4n-6 + 22:4n-6 + 22:5n-6)/(20:5n-3 + 22:5n-3 + 22:6n-3 + 20:3n-6 + 20:4n-6 + 22:4n-6 + 22:5n-6 + 20:3n-9).

Abbreviations: HUFA, highly-unsaturated fatty acid; DHA, Docosahexaenoic acid; EPA, eicosapentaenoic acid; AA, arachidonic acid; LA, linoleic acid.

Based on our current rates of recruitment, we expect to have a sufficient number of participants to complete the study 2 1/2 years after the first patient was enrolled. Based on these numbers, we should have adequate power to test our hypothesis of differential %n-6 HUFA in both plasma and erythrocyte lipid pools. Examination of the clinical data of the study (HIT-6, daily diaries) should allow us to predict effect sizes for a larger clinical trial.

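### Aim 2 models %n-6 in HUFA as a straight line in time, so diets that differ in onset but end at a similar level could be declared to have the same rate

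*Protocol article*

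**What the plan says.** Under Primary Outcomes, the protocol article sets the target: "For Aim 2, we examine the rate of change in %n-6 in HUFA over the 12 weeks of the intervention". Blood for this is drawn at four equally spaced visits, which are 0, 4, 8 and 12 weeks into the diet phase. The Analysis of Aim 2 then fixes the model. At the first level, "The first-level model specifies the outcome as a linear function of time". At the second, both the slope and the intercept are allowed to depend on the diet arm. The test is on the interaction: "The regression coefficients of the time-by-treatment terms are of interest here". The reading of a non-significant interaction is also fixed: "we will conclude that the rate of change in the outcome variable over time is the same in both groups". The Overview of the Statistical Analysis adds that the proportion will be transformed (angular, logit or power), without choosing one. Nothing in the article adds a curvature term, categorical visits or a shared baseline to this model.

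Table 5 gives the pooled erythrocyte course as mean and 95% CI at baseline and weeks 4, 8 and 12: "n-6 in HUFA* 76.3 74.5, 78.0 70.4 67.5, 73.2 67.4 63.7, 71.0 64.7 60.3, 69.0".

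**The concern.** Aim 1 already compares the arms at week 18, so what Aim 2 adds is the time course. A line through four equally spaced samples reduces that course to one number. Where the true course is fast and then slow, that number describes the average fall but not when the fall happened.

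Different onset is plausible here. Only one diet supplies EPA and DHA in quantity (Table 1), and in Table 5 pooled EPA has made 68% of its 12-week change by week 4.

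At stake is the conclusion of equal rates. It would be drawn from equal slopes, and two quite different curves can have equal slopes. A secondary issue is the intercept. Because it depends on the arm, misfit of the line can appear as a week-6 difference between randomised arms that have no true one.

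**Working it through.** **The plan's own figure.** The only design figure for Aim 2 is power close to 80% with 32 persons at four time points (Power calculations). It cannot be reproduced, because no slope difference, within-person correlation or significance level is given. The point does not depend on it.

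**Line through Table 5.** Inputs are the means 76.3, 70.4, 67.4 and 64.7 at intervention weeks 0, 4, 8 and 12. For complete balanced data, the mean slope of the mixed model equals the least-squares slope.
- Mean of the four values: 69.7.
- Sum of (t - 6)(y - 69.7) = -39.6 - 1.4 - 4.6 - 30.0 = -75.6. Sum of (t - 6)² = 80.
- Slope = -75.6/80 = -0.945 per week, or -3.78 per 4 weeks.
- Fitted baseline = 69.7 + 6 × 0.945 = 75.37, against 76.3 observed: 0.93 low, which is 8% of the 11.6-point fall.
- Average rate: 12 × 0.945 = 11.34, and 11.34/11.6 = 98%.

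| Interval (intervention weeks) | Observed fall | Observed rate per week | Fitted/observed |
|---|---|---|---|
| 0-4 | 5.9 | 1.475 | 0.64 |
| 4-8 | 3.0 | 0.75 | 1.26 |
| 8-12 | 2.7 | 0.675 | 1.40 |

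**Transformation.** The ratios in the last column become 0.60, 1.31, 1.52 on the logit scale, 0.62, 1.28, 1.46 on the angular scale, and 0.65, 1.25, 1.36 for the square root. The curve remains on each.

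**Why the slope does not see onset.** With four equally spaced visits, the slope per 4 weeks is 0.3 × first step + 0.4 × second + 0.3 × third; here 1.77 + 1.20 + 0.81 = 3.78. The first and last intervals carry equal weight, so reversing the order of the falls leaves the slope unchanged. Take three hypothetical arms that all go from 76.3 to 64.7:
- steady fall: slope -0.967 per week, fitted baseline 76.3;
- Table 5 shape: slope -0.945, fitted baseline 75.37, although the first-interval rate is 1.5 times the steady one (1.475/0.967);
- all of the fall by week 4: slope -0.3 × 11.6/4 = -0.870, fitted baseline 72.8, although the first-interval rate is 3 times the steady one (2.9/0.967).

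The earlier the fall, the slightly slower the arm appears.

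**Power.** Simulation with 32 per arm, complete data and assumed SDs (between-person 3.7, response 4.0, residual 1.5):
- Arms identical, Table 5 shape: the slope test rejects 5.0%.
- Same shape, 12-week falls of 10 and 13: power 0.74 for the slope, 0.73 for change at week 12, 0.57 for a 3-df visit-by-diet test.
- Same week-18 level, Table 5 shape against a straight line: about 6% for the slope, about 99% for a piecewise model with common baseline.
- Price of making the piecewise test primary when the arms share one shape: about 0.76 falls to about 0.67.

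**Spurious baseline difference.** If both arms have the Table 5 shape, it is 0.08 × the arm difference in 12-week change: 0 for equal changes; 0.08 × 11.6 = 0.93 points for falls of 5.8 and 17.4; 0.08 × 23.2 = 1.86 points for falls of 0 and 23.2.

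**Strength of the curvature.** The quadratic contrast is 76.3 - 70.4 - 67.4 + 64.7 = 3.2 points. With standard errors from the Table 5 intervals, t is about 1.3-1.4, 1.7-1.9, 2.1-2.3 or 2.9-3.2 for an assumed within-person correlation of 0.5, 0.7, 0.8 or 0.9.

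**The case against.** The strongest defence is that the stated target is the rate over 12 weeks, not the rate per interval. For that target the line does well: it recovers 98% of the average change, holds its 5% level under equal curves, and loses no power against week-12 change when the arms share a shape. The abstract asks for a greater decline, not an earlier one. All of this stands, and it rules out calling the Aim 2 test invalid. It does not rescue the decision rule, which speaks of the rate of change over time being the same and not of equal average decline.

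It can also be said that checking the form of a growth model is work for the SAP. That would be so had the article left it open, but the article fixes both the line and the conclusion.

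The evidence for curvature is thin: 20 participants, both diets combined, erythrocytes only, and a precision that depends on an unreported correlation. This stands, and limits confidence in the size of the effect.

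Three stronger readings are tempting and are not supported.
- That curvature must create a false baseline difference. Curvature common to both arms shifts both intercepts equally; a difference needs arms that differ in amount or shape of change, which pooled data cannot show. The plan also tests the interaction, not the intercept.
- That the early plateau of LA in Table 5 ("LA 11.5 10.8, 12.1 9.5 8.8, 10.2 9.3 8.6, 10.0 9.5 8.8, 10.3") shows a large loss of information. LA has 18 carbons, does not enter %n-6 in HUFA, and is a secondary outcome with no linear model fixed for it.
- That plasma will level off sooner. The article gives no plasma figures, and its Limitations section says plasma and erythrocyte PUFAs may not reach equilibrium in 12 weeks.

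**Conclusion.** The point holds in a limited form. The linear-time model sits badly with the trial's own interim curve, in which the first 4-week fall is about twice each later one, on the raw scale and after the planned transformations. As a summary of average 12-week change the slope is sound, to within 2-3%. As a basis for declaring equal rates it is not, because it is nearly blind to a difference in onset between arms with a similar end level (about 6% power in the case simulated). The possible spurious baseline difference is small, about 8% of the arm difference in 12-week change under the Table 5 shape, and conditional on the arms differing.

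The interval figures follow from Table 5 alone. The power figures rest on the assumed variances, 32 per arm and complete data. Whether the two diets in fact differ in onset cannot be known from pooled data. No Aim 2 result is shown to be wrong; what needs changing is what the model can answer and what may be concluded from it.

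**What to change.** In the Analysis of Aim 2:
- replace the linear time term by visit as a categorical factor (weeks 6, 10, 14, 18), or by a piecewise-linear term with a knot at week 10;
- give the randomised arms a common week-6 mean in place of an arm-dependent intercept;
- name one primary contrast, the between-diet difference in the 12-week linear or average-rate contrast;
- report the diet differences in change over weeks 6-10 and 10-18 as supporting contrasts;
- limit the conclusion from a non-significant primary contrast to this: no difference in average 12-week rate was shown. It should not say that the time courses are the same.

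No samples or visits change. The cost is a few extra parameters. Power would fall (about 0.76 to 0.67 for the piecewise test when the arms share one shape, and 0.74 to 0.57 for a 3-df test with falls of 10 and 13) only if a multi-df test were made primary, and keeping the single contrast avoids that. Because the interim data were analysed pooled and masked, the change can be made before the arms are compared.

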#### Power calculations

Assuming that the %n-6 in HUFA will be on average 0.8, 0.5 and 0.3 at the end of the 12 weeks (as predicted by Lands empirical equation [31] and the nutrient intake targets) and a common standard deviation set at the maximum value of 0.5, we determined that, to achieve 80% power, we need 32 individuals per each arm. Repeated measures power-analysis procedures indicate that we will have adequate power (close to 80%) to test the time interaction effect with 32 persons measured over 4 time points (Aim 2).

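### The Aim 2 growth model is valid, but it estimates a week-6 diet difference that randomisation makes zero in expectation, so it may give up some power for the diet-by-time test

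*Protocol article*

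**What the plan says.** Analysis of Aim 2 (Statistical Analysis) uses the "repeated measures of the outcome variable measured at 6, 10, 14, and 18 weeks". Its structure is written out: "The first-level model specifies the outcome as a linear function of time", and then "In the second level, the slope and intercept will be a linear function of the treatment variable". The test is on the interaction: "The regression coefficients of the time-by-treatment terms are of interest here". No equal-intercept constraint and no baseline covariate is stated for this aim.

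On timing, Interventions says "They have blood drawn for biomarkers at the first intervention visit (Week 6), and again at weeks 10, 14, and 18". Randomization places allocation at the first treatment visit, Analysis of Aim 1 says the week-6 specimen is given at randomisation, and Primary Outcomes calls week 6 pre-intervention and restates the schedule as "Weeks 0, 4, 8, and 12 of the intervention phase".

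The Aim 1 regression, by contrast, compares the diets "adjusting for covariates, including the baseline proportion and other variables that may influence the accumulation and turnover of LA in adipose tissue". Power calculations puts the power of the Aim 2 interaction test near 80% with 32 persons and four time points, without giving a correlation, a slope difference or variance components.

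**The concern.** The week-6 value precedes the diets, so its population mean is the same in both arms by design. A model with a free diet effect on the intercept estimates that known zero from the data. The errors of the estimated intercept and slope differences are in general correlated, so estimating the first adds variance to the second. Transient week-6 noise that happens to be high in one arm makes that arm's fitted decline look steeper.

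The slope difference is the only stated test for Aim 2, and its planned power is only about 80%. Any precision recoverable from samples already collected is worth having.

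**Working it through.** **Inputs from the article.** Four equally spaced visits; linear time; 1:1 allocation; 32 per arm (Power calculations says 32 per arm for Aim 1 and 32 persons for Aim 2; I take 32 per arm for both); SD 0.5; means 0.8, 0.5 and 0.3; the Table 5 means and confidence intervals. **Assumed:** two-sided 5% level, normal approximation, and every covariance parameter.

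**The plan's own figure.** With time scaled so that 12 weeks = 1 and compound symmetry with correlation ρ, the free-intercept variance of the 12-week slope difference is 3.6(1−ρ)σ²/n. For σ = 0.5, n = 32 and a difference of 0.3 (0.8 versus 0.5):

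- ρ = 0.5: SE 0.119, power 72%
- ρ = 0.6: SE 0.106, power 81%
- ρ = 0.7: SE 0.092, power 90%

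For a difference of 0.2 (0.5 versus 0.3), ρ = 0.8 gives 76%. The claim of about 80% is therefore attainable, but it cannot be reproduced without an assumed correlation. The comparisons below start from exactly 80% (standardised effect 2.80).

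**Cost of the free intercept.** Let a and b be the SDs of the random intercept and of the random 12-week slope, r their correlation and e the residual SD. For visits at 0, 1/3, 2/3 and 1, the per-person covariance of the fitted intercept and slope has

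- m00 = a² + 0.7e²
- m01 = rab − 0.9e²
- m11 = b² + 1.8e²

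The free model has variance proportional to m11, and the constrained model to m11 − m01²/m00. The ratio is 1 − m01²/(m00·m11), which never exceeds 1. New power = Φ(2.80/√ratio − 1.96).

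**Random intercepts only (b = 0).** The ratio becomes 1 − 9(1−ρ)/(14+6ρ).

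| ρ | ratio | power from 80% |
|---|---|---|
| 0.5 | 1 − 4.5/17 = 0.735 | 90% |
| 0.7 | 1 − 2.7/18.2 = 0.852 | 86% |
| 0.9 | 1 − 0.9/19.4 = 0.954 | 82% |

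**Random slopes.** Table 5 suggests spread that grows with time. SD = half-width × √n / t gives 1.75 × √20/2.093 = 3.7 at baseline and 4.35 × √18/2.110 = 8.7 at week 12. Both diets are pooled, so the week-12 figure includes any diet difference and only loosely guides the within-arm SD. Taking a = 3 and e = 2.2 (baseline SD 3.7):

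| b | r | week-12 SD | ratio | power from 80% |
|---|---|---|---|---|
| 7.5 | 0 | 8.4 | 0.976 | 81% |
| 7.5 | −0.3 | 7.5 | 0.847 | 86% |
| 7.5 | −0.5 | 6.9 | 0.697 | 92% |
| 6 | +0.3 | 7.8 | 0.998 | 80% |
| 4 | 0 | 5.5 | 0.938 | 82% |
| 4 | −0.5 | 4.2 | 0.650 | 94% |

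Example, first row: m00 = 9 + 3.388 = 12.388; m01 = −4.356; m11 = 56.25 + 8.712 = 64.962; ratio = 1 − 18.97/804.7 = 0.976. A larger residual share (a = 2.5, b = 5, e = 2.8, r = −0.5) gives 0.614, or 95%. A negative r means that people who start higher fall further.

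**Curvature.** Table 5 falls by 5.9, 3.0 and 2.7 points. If the diet difference had that shape (0, 5.9, 8.9, 11.6), the straight-line fit would have slope 11.34 and intercept 0.93. The constrained estimate targets 11.34 − (m01/m00) × 0.93. With a = 3, b = 7.5, e = 2.2 and r = +0.3, m01/m00 = 0.193, so the target is 11.16; with ratio 0.993, power is Φ(2.80 × 0.984/0.9965 − 1.96) = 79%. With compound symmetry at ρ = 0.5, m01/m00 = −0.53, the target is 11.83, and power is about 93% instead of 90%.

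**The case against.** The strongest reply is that slope and intercept both depending on treatment is the textbook growth-curve model. It is unbiased, keeps its type I error and contradicts nothing else in the article. That stands.

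A reader might infer that the baseline value goes unused in Aim 2, or that chance imbalance is left uncorrected. The text does not support this. Week 6 is the first of the four outcomes and the slope is a within-person contrast, so a persistent difference between arms cancels. Only the transient part of week 6, or a link between starting level and later change, reaches the slope.

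A reader might also take the rise from 80% to 90% as the size of the loss. That needs random intercepts only and a correlation of 0.5. Table 5 does not favour constant variance. With random slopes, zero intercept-slope correlation and modest residual variance, the gain is about a point.

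A further objection is that a straight line's intercept equals the week-6 mean only if change is linear, and Table 5 shows deceleration. This is fair in principle. Curvature of that shape cost about 1 point in the unfavourable case above and helped in the other, so it does not defeat the change.

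**Conclusion.** The point holds as one of efficiency. The Aim 2 model as written estimates a diet difference at week 6 that is zero in expectation. Under the stated linear model, constraining it never raises the variance of the diet-by-time coefficient. It also leaves type I error intact, because randomisation guarantees the constraint.

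The size is uncertain because the article gives no within-person covariance. From an 80% start it ranges from almost nothing to roughly 14 points, and the low end is as plausible as the high end. The calculations rest on 32 per arm, complete data, linear change and a two-sided 5% level. The Table 5 figures are untransformed erythrocyte values from 20 participants with the diets pooled, so they guide the covariance only roughly. The documents do not support calling the planned analysis biased or invalid.

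**What to change.** In Analysis of Aim 2, replace the second-level sentence with wording such as: *the slope will depend on treatment; the mean at week 6 will be constrained to be equal in the two diets because it precedes the intervention, and week 6 will remain in the likelihood as the first outcome.* Participants with missing later samples then still contribute.

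Do not substitute a model of weeks 10, 14 and 18 with week 6 as a covariate while testing the same interaction. Its time-by-diet term covers only weeks 10 to 18. It omits the first four weeks, where the pooled fall in Table 5 was largest (76.3 to 70.4), and so is not the 12-week rate that Aim 2 defines.

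The cost is one sentence, with no new data or visits. The small downside is somewhat more reliance on the linear time shape: about 1 point of power either way if the diet difference is curved and intercepts and slopes are positively correlated.
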